### RCT secondary objectives

To estimate comparative cost-effectiveness (cost/quality-adjusted life-years, QALY) of the two trial treatments, from an National Health Service (NHS) and personal social services perspective.To determine the difference in complication rate (eg, shoulder redislocation) in the first 12 months between the trial treatment groups.To quantify and draw inferences between the functional status (OSIS) of the trial treatment groups at 6 weeks, 3 and 12 months.To quantify and draw inferences on observed differences in the functional status (Disabilities of the Arm, Shoulder and Hand) of between the trial treatment groups at 6 weeks, 3, 6 and 12 months.To quantify and draw inferences on observed differences of health-related quality of life (EQ-5D-5L) between the trial treatment groups at 6 weeks, 3, 6 and 12 months.To qualitatively explore participants’ experiences of receiving the trial treatments and identify facilitators and obstacles to adhering to them.

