### Sample size

#### RCT sample size

A worthwhile difference from this intervention is four points on the OSIS.^8 9^ The SD of the OSIS 6 months after injury is 10 points.^8 9^ However, the literature has predominantly included a young population, given that we will recruit a wider range of ages a larger SD is expected, therefore an SD of 12 is more likely. To show a four-point difference at 5% significance level with 90% power allowing a margin of 20% loss during the follow-up needs a minimum of 478 participants.^5 9^

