#### Postrandomisation withdrawals

Participants may discontinue at any time without prejudice. Unless a participant explicitly withdraws consent, data will be collected until the end of the trial. For participants explicitly withdrawing consent for follow-up procedures, trial data obtained up until the point of withdrawal will be included. Participants will have the option to withdraw from the trial-related questionnaires, but continue to provide routine NHS data for trial purposes. Participants who withdraw will not be replaced. Participants may be withdrawn from the trial at the discretion of the investigator and/or trial steering committee for safety concerns.

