To address the possibility that these might exist, a single interim analysis is preplanned to re-estimate the sample size. This will occur after approximately 200 participants have completed the 3 months follow-up questionnaire, while recruitment is still open. The pooled SD of the primary outcome and presence of therapist effects will be estimated by calculating the therapist intraclass correlation coefficient and its 95% CI. Models will not include treatment effects. A revised sample size calculation will be discussed with DMC and TSC and if appropriate, permission requested from the funder to adjust the sample size.

All primary analyses are planned to be on an intention-to-treat basis with secondary per protocol analyses. The main analysis will investigate differences in the primary outcome measure, 6 months after randomisation, between the two treatment groups. Unadjusted and adjusted regression analyses will be used to estimate the between group difference. The adjusted analyses will adjust for the stratification variables, baseline scores and any other clinically important variables. Since individual clinicians will treat only a small number of participants enrolled in the trial, we do not expect clinician-specific effects to be important in this study.

Descriptive statistics of functional outcome data (ie, QuickDash and EQ-5D-5L) at each time point will be constructed with between group analyses following the method set out for the primary analysis above. Patterns of recovery will also be explored. Secondary analyses will includeχ^2^ tests to compare the number of dislocations and other complications between allocation groups. For important complications (eg, dislocations), Kaplan-Meier curves of the time to complication will be constructed. If sufficiently large numbers of complication groups are observed, Cox regression models will be constructed to compare the time to complication in each arm. Temporal effects will be investigated using a multilevel model of all follow-up data.

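### The only between-arm test of 12-month redislocation and complications that is certain to be run is a chi-square on counts; the time-to-event comparison depends on an undefined condition set by the data

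*Protocol article*

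**What the plan says.** The protocol article gives the objective under RCT secondary objectives: "To determine the difference in complication rate (eg, shoulder redislocation) in the first 12 months between the trial treatment groups".

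Under RCT statistical analysis it names three analyses for it:

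- **Chi-square, unconditional.** χ² "tests to compare the number of dislocations and other complications between allocation groups". The denominator is not stated.
- **Kaplan-Meier, unconditional for important complications such as dislocation.** "Kaplan-Meier curves of the time to complication will be constructed". No log-rank test, 12-month risk or risk difference is attached.
- **Cox regression, conditional.** "If sufficiently large numbers of complication groups are observed, Cox regression models will be constructed to compare the time to complication in each arm". No number of events is given for the condition.

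Two other sections bear on length of follow-up. The RCT sample size is described as "allowing a margin of 20% loss during the follow-up needs a minimum of 478 participants". For people who withdraw consent to follow-up, Postrandomisation withdrawals says that "trial data obtained up until the point of withdrawal will be included".

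For comparison, the SWAT analysis section pairs its own Kaplan-Meier curve, for time to questionnaire return, with a log-rank test and an adjusted Cox model, neither of them conditional.

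**The concern.** The objective is a rate over a fixed 12 months, and some participants will be observed for only part of it. A two-by-two table has no natural cell for a person who is event-free at 3 months and then lost. There are three ways to force such people into the table:

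- **(a)** Keep everyone randomised and count losses as event-free. Risks are understated, more so in the arm with more loss.
- **(b)** Keep only 12-month completers. Events already reported by people who later left are thrown away, which sits badly with the rule that data up to withdrawal are included.
- **(c)** Keep all reported events and the event-free completers. Risks are overstated, more so in the arm with more loss.

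Kaplan-Meier, log-rank and Cox methods use the partial follow-up directly. The plan already draws the curves, but leaves the matching comparison to a condition judged after the events have been seen. At stake are the size of the reported redislocation difference and, if retention differs between arms, a modest distortion of its test.

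**Working it through.** **The plan's own figure.** Inputs from RCT sample size: "To show a four-point difference at 5% significance level with 90% power allowing a margin of 20% loss during the follow-up", and "an SD of 12 is more likely". Per arm, n = 2(1.96 + 1.2816)² × 12²/4² = 2 × 10.507 × 9 = 189.1, so 190. The total is 380, and 380/0.8 = 475 (476 with whole numbers per arm). The stated 478 is reproduced to within 1%, giving 239 per arm. No event rate or power is stated for redislocation, so every event risk and every loss pattern by arm below is an assumption.

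**Set-up.** 239 per arm, constant hazard, loss unrelated to outcome. If a proportion w_k is last seen at month t_k, denominator (a) observes an average risk of Σ w_k [1 − (1 − p)^(t_k/12)], where p is the true 12-month risk. Last contact is at 0, 1.4, 3, 6 or 12 months, with losses before month 6 split evenly over the first three.

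**Equal loss: 20% missing at 6 months, 30% at 12; true risks 20% v 10%.**

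- At p = 0.20 the risk reached by 1.4, 3, 6 and 12 months is 0.0257, 0.0543, 0.1056 and 0.2000. Observed: (0.20/3)(0.0257 + 0.0543) + 0.10 × 0.1056 + 0.70 × 0.20 = 0.156.
- At p = 0.10 the same sum is (0.20/3)(0.0122 + 0.0260) + 0.10 × 0.0513 + 0.70 × 0.10 = 0.078.
- Difference under (a): 7.8 points instead of 10.0.
- Simulated power: (a) 77.8%, log-rank 77.8%. Completers only (b): 74.5%, against about 78% for log-rank. Denominator (c) overstates the difference at about 10.9 points.

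With the protocol's 20% loss carried to 12 months, spread evenly and equal in both arms, (a) gives about 9.0 points. Power is 83% for (a), 83% for log-rank and 78% for (b), and all three tests hold about 5% type I error.

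**Unequal loss, no true difference.** For the larger pattern, take advice with 25% missing at 6 months and 40% at 12, and physiotherapy with 15% and 20%. The shift under (a) is D, with SE = √[2p̄(1 − p̄)/239] and type I error ≈ Φ(−1.96 + D/SE) + Φ(−1.96 − D/SE).

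- Risk 20%: observed 0.1425 v 0.1693, D = 0.0268, SE = 0.0332, ratio 0.81; 0.125 + 0.003, about 13%.
- Risk 30%: observed 0.2150 v 0.2545, D = 0.0395, SE = 0.0388, ratio 1.02; 0.173 + 0.001, about 17%.
- Risk 10%: observed 0.0709 v 0.0845, D = 0.0136, SE = 0.0245, ratio 0.56; 0.080 + 0.006, about 9%.

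Simulation agrees:

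| Loss by 12 months | True risk, both arms | Type I error, (a) | Log-rank |
|---|---|---|---|
| 15% v 25% | 20% | 6.6% | 4.8% |
| 10% v 30% | 20% | 8.7% | 4.7% |
| 33% v 23% | 20-30% | 7-9% | about 5% |
| 40% v 20% | 3-5% | 5.7-7.1% | about 5% |
| 40% v 20% | 10% | about 9% | about 5% |
| 40% v 20% | 20-30% | 12-17% | about 5% |

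Under 40% v 20% loss, completers only (b) stays at about 5-6%, with a spurious difference of at most 0.1 point. Denominator (c) gives about 7.5% at 20-30% risks, with the bias in the opposite direction to (a).

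**Expected events in the worst cells.** 239 × (0.1425 + 0.1693) = 75 at 20% risk and 239 × (0.2150 + 0.2545) = 112 at 30%.

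**The case against.** The strongest reply is that the large distortions arise where the plan would probably run Cox anyway. About 75 to 112 events is ample for a two-arm Cox model, so the condition would most plausibly fail only when events are few. There, at 3-5% risk, even denominator (a) under 40% v 20% loss gives no more than about 7%. This stands as a plausible reading. It is not certain, because no threshold is written down.

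A reader might infer that the planned comparison is biased or underpowered as written. The documents do not support that. They state neither the denominator nor retention by arm. With equal loss, the all-randomised chi-square keeps its error rate and matches log-rank for power. With completers only, unequal loss produces no bias as long as loss is unrelated to outcome.

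A reader might also infer that retention will differ because one arm has more contact. That is possible in an unblinded trial, but follow-up is run centrally, treating clinicians take no part in it, and advice participants may seek further physiotherapy.

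There are mitigations too. The Kaplan-Meier curves are unconditional. Participants who leave the questionnaires may still allow use of routine NHS data. Multiple imputation is possible. Neither of the last two is tied to complications, so they may reduce the problem but cannot be relied on to remove it.

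Finally, the choice of denominator is usual content for the analysis plan, which is not shown. Its absence here is therefore no fault. What remains is what the article does state: an unconditional test that ignores length of follow-up, and a better one subject to an open condition.

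**Conclusion.** The point holds as a small, inexpensive improvement to a secondary analysis. The analysis is not wrong as written. The chi-square on counts is the only between-arm comparison of 12-month complications sure to be run, and the method that uses partial follow-up depends on an undefined, data-driven condition.

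The most predictable consequence is in the estimate. Under equal loss, counting losses as event-free turns 10.0 points into about 9.0 (20% lost) or 7.8 (30% lost). Using completers only costs about 4-5 points of power and discards reported events. A raised false-positive rate needs loss that differs between arms and a denominator other than completers only. Under (a) it is about 7-9% in most scenarios tried, and 12-17% only at 40% v 20% loss with 20-30% risks.

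These sizes rest on assumed event risks, assumed loss patterns, a constant hazard and loss unrelated to outcome.

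**What to change.** In RCT statistical analysis, for first redislocation and other important complications with a date:

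- make a log-rank or unadjusted Cox comparison, censored at last contact, unconditional;
- report the Kaplan-Meier 12-month risk in each arm and the risk difference with 95% CI;
- remove the condition on event numbers for this unadjusted comparison;
- keep the chi-square as supportive, with its denominator stated.

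The cost is wording only. The planned curves already need event and censoring dates, and the SWAT section already follows this pattern. There are two drawbacks to accept: the hazard ratio will have a wide interval if events are few, and log-rank, Cox and Kaplan-Meier all still assume non-informative censoring, so losses by arm should be reported alongside.

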#### RCT health economic analysis

A prospectively planned analyses will be detailed in a health economic analysis plan, agreed with the DMSC. Analysis will be conducted from an NHS and personal social services perspective, with methods adhering to the recommendations of the National Institute for Health and Care Excellence (NICE) reference case.^13^

Costs of the intervention groups will be estimated, reflecting resource inputs associated with rehabilitation and broader healthcare resource utilisation. Resource use associated with the index condition will be captured through routine health service data collection systems and participant questionnaires administered at each follow-up time point.

Unit costs will be estimated from local and national sources using established accounting methods, reflated to current prices. Health-related quality of life will be measured at baseline and at all follow time points using the EQ-5D-5L measure. Responses will be used to generate QALYs using the UK value set recommended by NICE guidance at the time of analysis.^14^

Within-trial analysis using bivariate regression of costs and QALYs, with multiple imputation of missing data, will inform a probabilistic assessment of incremental treatment cost-effectiveness. Missingness mechanisms will be explored and multiple imputation methods will be used where appropriate to avoid biases associated with complete case analysis. Findings will be analysed and visualised in the cost-effectiveness plane, as cost-effectiveness acceptability curves, net monetary benefit and value of information analysis. Costs and outcomes arising during the trial will be undiscounted, reflecting the 12-month time horizon. Sensitivity analyses will be undertaken to explore uncertainties and to consider issues of generalisability of the study.

#### SWAT analysis

All eligible participants will be included on an intention-to-treat basis, using two-sided statistical significance at the 5% level. We will summarise baseline characteristics of participants by the type of SWAT intervention sent. An average cost per participant will be estimated for each SWAT intervention arm. For the primary outcomes of questionnaire response rates, the difference in proportions will be calculated with 95% CIs, and the primary analysis will be a χ^2^ test to assess statistical association. Additionally, a logistic regression adjusting for age, gender and host trial treatment allocation will be performed to investigate the effects of these variables. A per-protocol analysis will also be performed.

The secondary outcome of time to questionnaire return will be assessed by a Kaplan-Meier curve and the SWAT interventions compared by log rank test. Cox regression will be applied adjusting for participant age, gender and host trial treatment allocation, and the effect of the intervention reported. The requirement for any questionnaire return reminder will be analysed in the same way as the primary outcome).

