#### SWAT sample size

The sample size for the SWAT is limited by the host trial sample size. The SWAT opened to recruitment after the internal pilot (50 participants), therefore, approximately 428 participants (214 per group) are expected and would provide 90% power and 5% significance to detect differences in retention rates of approximately 11%.

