#### SWAT randomisation

Minimisation with a random factor will be used to avoid imbalance between the SWAT intervention arms. The allocation ratio will be 1:1 and stratified by the ARTISAN allocation arm. Allocation concealment will be maintained by an independent randomisation team who will be responsible for generation of the sequence and have no role in the allocation of participants.

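### The SWAT is balanced on host-trial arm but its primary test and interval ignore that factor; the test stays valid, and stratifying by host arm gains a little precision without new data

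*Protocol article*

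**What the plan says.** Under SWAT randomisation, the protocol article states: "Minimisation with a random factor will be used to avoid imbalance between the SWAT intervention arms". It continues: "The allocation ratio will be 1:1 and stratified by the ARTISAN allocation arm". No other balancing factor is named for the SWAT.

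Under SWAT analysis, the comparison is by intention to treat, "using two-sided statistical significance at the 5% level". For questionnaire return, "the difference in proportions will be calculated with 95% CIs" and "the primary analysis will be a χ^2^ test to assess statistical association". Neither is said to take account of host arm. Host arm appears only in a further step: "a logistic regression adjusting for age, gender and host trial treatment allocation will be performed to investigate the effects of these variables". The need for reminders is to be handled in the same way as the primary outcome, so the choice carries over to that outcome.

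Under SWAT sample size, "approximately 428 participants (214 per group) are expected", with a stated 90% power at the 5% level for a difference of about 11 points.

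For the host trial, RCT statistical analysis plans both unadjusted and adjusted regressions, the adjusted ones including the stratification variables.

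**The concern.** When allocation is balanced on a factor that predicts the outcome, the difference between arms varies less from sample to sample than an unstratified standard error assumes. An analysis that ignores the factor therefore gives p-values that tend to be too large and an interval that is too wide. Here the factor is host arm.

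Different return by host arm is conceivable. One host arm is offered extra physiotherapy sessions for up to 4 months and the other a single advice session, and participants know which they have been given. The article gives no figure for such a difference.

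The SWAT cannot enlarge its sample, because its size is set by the host trial, so precision lost through the choice of analysis cannot be regained by recruiting more. A model containing host arm is already planned, but its stated purpose is to look at the covariates, and it does not supply the primary result.

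**Working it through.** **Inputs.** 214 per SWAT arm, two-sided 5%, 90% power and about 11 points come from SWAT sample size and SWAT analysis. An 80% return rate is an assumption, borrowed from the 20% loss allowance in the host trial's sample size; the SWAT section states no base rate. The gap in return between host arms is not given, so a range is assumed. Host arm is taken as exactly balanced: 428/4 = 107 in each SWAT-by-host cell.

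**The plan's own figure.** Power for 80% versus 91% with 214 per group (pooled variance, no continuity correction) is 0.901, and the size needed for 90% power is 214 per group. The stated figure reproduces.

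**Effect of ignoring host arm.** With mean return p = 0.80, the unadjusted variance per participant is p(1 − p) = 0.80 × 0.20 = 0.16. With host-arm rates p ± g/2, the relevant variance is the mean of the two within-arm values. For a 10-point gap this is (0.75 × 0.25 + 0.85 × 0.15)/2 = (0.1875 + 0.1275)/2 = 0.1575. For a 20-point gap it is (0.70 × 0.30 + 0.90 × 0.10)/2 = (0.21 + 0.09)/2 = 0.15.

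True type I error of the unadjusted test = 2 × [1 − Φ(1.96/√(within/0.16))]. CI half-width = 1.96 × √(variance × 2/214).

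| Assumed gap (points) | Within-arm variance | Ratio to 0.16 | True alpha | Half-width, unadjusted | Half-width, stratified |
|---|---|---|---|---|---|
| 0 | 0.1600 | 1.000 | 0.050 | 7.58 | 7.58 |
| 5 | 0.1594 | 0.996 | 0.0496 | 7.58 | 7.56 |
| 10 | 0.1575 | 0.984 | 0.048 | 7.58 | 7.52 |
| 15 | 0.1544 | 0.965 | 0.046 | 7.58 | 7.44 |
| 20 | 0.1500 | 0.938 | 0.043 | 7.58 | 7.34 |
| 30 | 0.1375 | 0.859 | 0.035 | 7.58 | 7.03 |

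The unadjusted variance is thus overstated by 0.16/0.1575 = 1.016 (1.6%) at a 10-point gap and by 0.16/0.15 = 1.067 (6.7%) at 20.

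**Power.** This was simulated with 200,000 runs and 107 per cell, comparing the Pearson chi-square with a Mantel-Haenszel test stratified by host arm.

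- 11-point effect centred on 80%: 82.1% versus 82.3% at a 10-point gap, and 82.6% versus 84.1% at 20.
- At a 30-point gap: 81.4% versus 85.2%. This is approximate, because one cell had to be capped just below 100%.
- 80% versus 91%: 91.0% versus 91.3% at a 10-point gap, and 91.3% versus 92.1% at 15.

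The level near 82% reflects where the 11 points are placed, not the choice of test. Under no SWAT effect, the simulated size at a 20-point gap was 0.043 for the chi-square and 0.050 for the stratified test.

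**The case against.** The strongest reply is that nothing here is invalid. The chi-square keeps its type I error at or below 5%, the sample size was evidently worked out for the same unadjusted comparison, and the adjusted model is prespecified in the same section. On that view, the ranking of the two analyses is a matter of preference.

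There is also little in the article to suggest a large gap. Follow-up is run centrally for everyone, treating clinicians take no part in it, and the extra sessions end by 4 months, before the 6-month questionnaire. A reader might picture the advice arm as discharged and out of contact. The article does not say so: those participants are told whom to contact if they are not improving, and further physiotherapy that they initiate themselves is allowed.

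Most of this stands and limits the point to a minor improvement. It does not remove the mismatch between how the SWAT is allocated and how its primary result is computed, and the remedy costs almost nothing.

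A reader might also credit the correction with the full gain from adjusting for age and gender. With an assumed 10-point host gap plus a 20-point age or gender gap (cells 0.95, 0.85, 0.75, 0.65), the within-cell variance is 0.1475 and the ratio 0.16/0.1475 = 1.085. But of the between-cell variance of 0.0125, host arm supplies 0.05² = 0.0025 and age or gender 0.10² = 0.0100, or four fifths. Age and gender are not SWAT balancing factors, so leaving them out does not distort the test's error rate. It only forgoes optional precision.

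**Conclusion.** The point holds as a small, free improvement. If return depends on host arm, the primary SWAT test is slightly conservative and the interval for the difference slightly too wide. At an assumed 80% return, an assumed 10-point gap makes the interval about 0.8% too wide (7.58/7.52) and costs about 0.3 points of power. A 20-point gap makes it about 3% too wide (7.58/7.34) and costs about 1.5 points. The loss exceeds 2 points of power only somewhere between a 20- and a 30-point gap.

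Two stronger readings are tempting and not supported. One is that the SWAT's test is invalid or its false-positive rate inflated; the error runs the other way. The other is that the stated 90% power fails for this reason; it reproduces for 80% versus 91%, and host arm barely moves it. All sizes rest on the assumed return rate, the assumed gaps and near-exact balance on host arm.

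**What to change.** Make the primary 6-month SWAT comparison account for host arm, in one of two ways:

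- a Mantel-Haenszel test with a risk difference stratified by host arm and its 95% CI; or
- a risk difference standardised over the sample from the planned logistic model (SWAT arm, host arm, age, gender), with its 95% CI.

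Promoting the logistic model by itself is not enough. It yields a conditional odds ratio, which does not narrow the interval for the difference in proportions. Keep the unadjusted difference and chi-square as supportive, and apply the same order to the reminder outcome, which follows the primary analysis. Including age and gender is an optional further gain in precision.

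The cost is a short change to the analysis text and a little extra programming. Data collection, randomisation and sample size are unaffected. The change should be fixed before return is compared by SWAT arm.
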